### Sample size

There is no specific hypothesis for the primary outcome in our cohort study, thus, the sample size is estimated based on the number of variables, using the method recommended for registry study (10 times number of variable) [39]. The sample size is estimated as at least 450, and increases to 495 for 10% loss during follow-up.

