## Background

Stroke leads to millions of death and disability in China and other countries annually [1, 2]. To optimize stroke management and improve functional outcome, causative mechanism of stroke is of great importance. Branch Atheromatous Disease (BAD), first described by Caplan in 1989 [3], is increasingly becoming a clinical entity with the aid of neuroimage, characterized by stenosis or occlusion at the origin of a penetrating artery resulting from atherosclerosis and leading to ischemic lesion [4]. In our study, the term “Branch Atheromatous Disease (BAD)-related stroke” is used for ischemic stroke due to branch atheromatous disease.

Although proposed as a meaningful concept, BAD remained neglected and underused in clinical practice, researches and guidelines for the past three decades [4]. Epidemiological data on BAD is spare, and most studies were reported in Asian population [4]. Small vessel occlusion or intracranial atherosclerosis are more common in Asians, which is different from Western populations. BAD-related stroke accounted for 9.1% in Japan and 20.4% in Hongkong among ischemic stroke patients [5, 6]. Perforating arteries involve lenticulostriate artery (LSA), paramedian pontine artery (PPA), thalamoperforating artery, anterior choroidal artery and Heubner's artery [4, 6], while what have been widely studied Is LSA and PPA, indirectly via features of ischemic lesions [4, 7]. Based on clinical and neuroimage evidence, neurologists and researchers have proposed the diagnostic criteria for BAD-related stroke [7–9].

Of patients with BAD-related stroke, the mean age ranged from 54 to 75 years, slightly younger than that in large artery disease (LAD) or lacunar infarction (LACI), and male gender was more prevalent [4, 6, 10]. The median National Institutes of Health Stroke Scale (NIHSS) score of BAD-related stroke was 4, lower than 6 in LAD, but similar with that in LACI. The short-term disability (modified ranking scale [mRS] ≥ 3) rates of LAD, BAD-related stroke, and LACI were 74%, 61%, and 47%, respectively [6]. However, long-term outcomes were comparable between BAD-related stroke and LACI [11]. Finally, the clinical, neuroradiologic, and predictive data are insufficient for BAD-related stroke.

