### Statistical analysis

Categorical variables will be presented as frequencies and percentages, such as gender, vascular risk factors, lesions of penetrating artery, and therapies. Continuous variables with non-normal distributions will be shown as median and interquartile range (IQR), while continuous variables with normal distributions as mean and 95% confidence interval (CI), such as age, NIHSS score, blood pressure, and hemoglobin concentration. For the statistical significance analysis of the outcomes, Pearson χ 2 or Fisher’s exact test, Wilcoxon tests, and t-tests will be used, where appropriate, with statistical uncertainty expressed by means of 95% CI. Cox proportional hazards model, Logistic regression model, and Poisson regression model will be used to assess the association between outcomes and clinical or radiological predictors, where appropriate. The good prognosis is defined as 0–2 mRS score, and poor prognosis as 3–6 mRS score at 90 days. Predictors including clinical and radiological features and different treatments will be evaluated. All analysis will be performed using SAS 9.4 and two-sided *P* < 0.05 is considered significant.

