## Discussion

BAD-study will be the first prospective clinical-radiological cohort with long-term follow-up and large sample, focusing on the BAD-related stroke, a neglected but clinically meaning subtype of stroke in Asians with poor collateral circulation and high disability [4, 10, 40]. The demographic clinical, radiological, and prognostic characteristics of BAD-related stroke in China will be reported.

In addition, we noticed that the BAD-related stroke was categorized as “stroke of undetermined etiology” in TOAST classification system, and thus failed to reflect its underlying stroke mechanism [4, 6, 40]. Our study will update the original TOAST classification, and prove the concept of BAD-related stroke. In addition, we noticed the higher frequency of cardiogenic embolism in elderly patients with lacunar infarcts, and excluded patients with cardiogenic stroke in our study [41].

With the documented data of laboratory tests, the role of inflammatory indicators on the prognosis of stroke will be assessed. The management of inflammatory indicators might be a novel therapy on reducing END and improving the outcome of BAD-related stroke [12, 28, 29, 31].

With the aid of MRI, MRA, HR-MRI, and ASL, BAD-study will analyze the cerebral artery, vessel wall of parent artery and penetrating artery, artery plaques, brain tissue, cerebral perfusion, and volume of lesion in BAD-related stroke. In addition, visualized analysis of LSA, and its association with outcomes will help neurologists understand the vascular mechanism of END [35, 42]. Radiological data of artery and lesion will provide clues for possible effective drugs. Moreover, quantitative analysis will be conducted to analyze the effect of lesion on the volume of gray matter and white matter, as global brain inflammation could be elicited by localized lesion [43, 44]

Besides, the comparison of different therapy strategies on primary outcome and END will provide direct clinical evidence to optimize the acute therapy in BAD-related stroke [13] and find the probably effective strategy of preventing END [12]. Based on the results of BAD-study, a risk prediction model will be generated for the prognosis, which may help neurologists individualize treatment strategy.

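### The sample-size rule counts patients per variable, but the binary-outcome models it must support are limited by the smaller outcome class, so 450 patients support at most about 22 candidate parameters, not the implied 45

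*Protocol article*

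**What the plan says.** The protocol article's Sample size section starts from the position that "There is no specific hypothesis for the primary outcome in our cohort study", and therefore that "the sample size is estimated based on the number of variables, using the method recommended for registry study (10 times number of variable". The result is given as: "The sample size is estimated as at least 450, and increases to 495 for 10% loss during follow-up". The number of variables is not stated, and no expected number of outcome events enters the calculation.

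The Statistical analysis section names Cox, logistic and Poisson regression for relating outcomes to clinical and radiological predictors, including treatments. It dichotomises the primary scale: "The good prognosis is defined as 0–2 mRS score, and poor prognosis as 3–6 mRS score at 90 days". END, a secondary outcome in the Outcome measures section, is defined as occurring or not within 7 days of enrolment. No linear or ordinal regression is named.

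A model for predicting outcome is among the secondary objectives, and the Discussion says that "a risk prediction model will be generated for the prognosis", with a view to individualising treatment.

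**The concern.** The size of the study has one justification, a ratio of 10 to the number of variables, and the 10 counts all patients. In regression on a yes/no outcome, the amount of information depends mainly on the less frequent outcome class. In a Cox model it depends on the number of events. A ratio of 10 patients per variable can therefore correspond to far fewer than 10 events per variable.

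If predictor numbers were set by the stated ratio, odds ratios would tend to be exaggerated, chance predictors would be selected, and predicted risks would be too extreme. That matters more here than in a purely descriptive registry, because the resulting model is meant to inform individual treatment. The pool of possible predictors is also wide: the clinical items in Table 1, the laboratory tests, and the plaque and vessel measurements.

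**Working it through.** **Inputs**
- Patients per variable 10, evaluable patients 450, loss 10%: Sample size section.
- Poor-outcome rate 61%: Background, where the short-term disability (mRS ≥ 3) rates for large artery disease, "BAD-related stroke, and LACI were 74%, 61%, and 47%, respectively". The smaller class is then good outcome, 39%. This is a background figure, not a planning assumption.
- END rate 13.8%: Background, for deterioration after intravenous thrombolysis, measured as an NIHSS worsening of at least 4 points at 24 h.
- Assumptions of this review: poor outcome of 20–30%, considered because the enrolled patients' median NIHSS is 3 (Table 3) against 4 in the Background; END up to 30%; explained variation of 15%, 30% or 50% of its maximum.

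**Step 1: reproduce the plan's figures.** 450 / 10 = 45 implied variables. 450 × 1.10 = 495, as stated. (Dividing by 0.90 would give 500, and 495 × 0.90 = 445.5; the difference is minor and is not the point here.)

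**Step 2: events per variable.** With outcome rate p, the smaller class is 450 × min(p, 1 − p). Divide by 45 for events per variable if all 45 entered one model. Divide by 10 and round down for the parameters supported at 10 events each.

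| Outcome rate | Smaller class | Events per variable, 45 variables | Parameters at 10 events each |
|---|---|---|---|
| 50% (best possible) | 225 | 5.0 | 22 |
| mRS 3–6 at 61% | 175.5 | 3.9 | 17 |
| 30% (assumed, mRS or END) | 135 | 3.0 | 13 |
| mRS 3–6 at 20% (assumed) | 90 | 2.0 | 9 |
| END at 13.8% | 62.1 | 1.4 | 6 |

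The first row is a ceiling. No outcome rate gives more than 5 events per variable for 45 variables in a binary-outcome model.

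**Step 3: cross-check by expected shrinkage.** The expected calibration slope S solves n = k / [(S − 1) ln(1 − R²/S)], with n = 450 and k = 45 unpenalised parameters. At 61% poor outcome the maximum R² is 1 − exp{2[0.61 ln 0.61 + 0.39 ln 0.39]} ≈ 0.74, so 15%, 30% and 50% of it are 0.111, 0.221 and 0.369.

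| Rate | S at 15% | S at 30% | S at 50% |
|---|---|---|---|
| mRS 3–6 at 61% | 0.55 | 0.73 | 0.83 |
| END at 13.8% | 0.48 | 0.66 | 0.77 |

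All six values fall short of the usual target of 0.9. Turned round, a slope of 0.9 with 450 patients allows about 5 to 23 parameters at 61% and about 4 to 16 at 13.8%, depending on the explained variation. This broadly agrees with step 2 and shows that 10 events per parameter can be lenient when predictors are weak.

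**The case against.** The strongest reply is that the 45-variable model does not exist in the document. The 45 is back-calculated, and it may be a count of items collected rather than of model terms. The article says only that the regressions will be used where appropriate. The sample of 450 meets the rule as written, which is attributed to a registry-study source that cannot be checked here and does not mention events. Predictor selection, penalisation and internal validation commonly sit in an analysis plan, which is not shown. The study is also largely descriptive, and its primary outcome is a 7-level score, which carries more information than a two-way split.

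Much of this stands. A reader might infer that the prediction model will be badly overfitted, or that the study must recruit far more patients. The documents support neither. A model with 17 or fewer parameters for 90-day mRS would meet 10 events per parameter at the 61% rate, and nothing in the article rules that out. The absence of a stated selection or validation method is not counted as a fault.

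Two things remain. An unseen analysis plan could protect the model, but it would not turn a patient count into the right basis for event-limited models. If far fewer than 45 variables are to be modelled, the stated derivation does not describe the analysis. And although the score is ordinal, the article dichotomises it and names no ordinal model, while END is binary in any case.

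**Conclusion.** The point holds in a conditional form. The rule counts patients, whereas the models the article names for its binary outcomes are limited by the smaller outcome class. The ceiling of 5 events per variable for the implied 45 depends on no assumed rate. The figures below it do:

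- 3.9 uses a short-term background disability rate that the article does not adopt for planning.
- 1.4 uses an END rate from thrombolysed patients under a narrower definition. This study also counts a motor increase of 1 point and follows patients to 7 days after enrolment, so its END rate may well be higher.
- The 20–30% poor-outcome range, the 30% END rate and the explained-variation values are assumptions, and the calibration slopes apply only to an unpenalised 45-parameter model.

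Overfitting is thus a risk that the stated rule permits, not a result that the plan guarantees. What needs correcting is the justification in the Sample size section and the number of predictors it implies. The enrolment target can stay.

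**What to change.** Keep the target of 450 evaluable patients (495 enrolled) and rewrite the justification:

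1. Apply the 10-to-1 rule to the smaller outcome class and state the expected number of events for each modelled outcome.
2. State what 450 patients then support: at most about 22 candidate parameters for any binary outcome; about 17 for 90-day mRS at 61% disability, or 9–13 at an assumed 20–30% poor outcome; about 6 for END at 13.8%, and up to 13 at an assumed 30%. Count parameters rather than variables, since a predictor with several categories uses more than one.
3. Limit the pre-specified candidate parameters to that number, chosen on clinical grounds before outcomes are examined, or use penalised regression for a larger set.
4. Report calibration and discrimination corrected for optimism, for example by bootstrap.

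This costs protocol or analysis-plan wording and some additional analysis, with no extra patients. The downside is a shorter list of candidate predictors and a less favourable statement of what 450 patients can support.

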### Outcome measures

The primary outcome in our study is the score on the modified Rankin scale at 90 days, which is a 7-point scale ranging from 0 (no symptoms) to 6 (death) [36]. Secondary outcomes include END within 7 days, and NIHSS score, Barthel index, cerebrovascular events (myocardial infarction, new-onset ischemic stroke, new-onset intracranial hemorrhage), and major bleeding complications measured by PLATO (Platelet Inhibition and Patient Outcomes) definition during 90-day follow-up [37]. All-cause mortality within 90 days is also recorded. The follow up times are extended to 1 year, as the long-term outcome of BAD-related stroke remains inconclusive [4, 6].

The END is defined as: 1) From symptom onset to 7 days after enrollment; and 2) Occurrence of deterioration of neurologic deficits after initial assessment: A. An increase of the NIHSS score ≥ 4 points or the NIHSS motor score ≥ 1 point for ischemic patients; or B. The stereotyped attacks still repeat ≥ 3 times after arrival at hospital or progress to persistence status for patients with internal capsule warning syndrome or pontine warning syndrome [12, 38].

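### The 495 enrolment target, set for 10% loss, would leave about 445 patients with follow-up, about 5 (1%) below the stated minimum of 450

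*Protocol article*

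**What the plan says.** The Sample size section of the protocol article explains that no hypothesis test drives the number: "There is no specific hypothesis for the primary outcome in our cohort study". The size comes instead from a rule tied to the count of variables, "using the method recommended for registry study (10 times number of variable"). The section then sets a floor and an enrolment figure in one sentence: "The sample size is estimated as at least 450, and increases to 495 for 10% loss during follow-up".

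The section gives neither the number of variables nor the formula used for the inflation. No other section gives a different enrolment target.

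The Outcome measures section fixes the endpoint that depends on follow-up: "The primary outcome in our study is the score on the modified Rankin scale at 90 days".

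**The concern.** Three figures appear together: a minimum of 450, an enrolment of 495 and a loss of 10%. An allowance for loss is meant to ensure that the required number is still available once the expected loss has occurred. Because loss is a share of those enrolled, the required number should be divided by the retained share. Adding 10% to the required number gives a smaller allowance than the stated loss rate calls for.

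The loss bears on the primary outcome. A patient lost before day 90 has no observed modified Rankin score and cannot contribute an observed outcome to the regressions in the Statistical analysis section. What is at stake is whether the stated enrolment delivers the stated minimum at the stated loss rate. With no power calculation in the plan, nothing further depends on it.

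**Working it through.** **Inputs, all from the Sample size section**
- Required number: N = 450, given as a minimum.
- Loss during follow-up: d = 10%.
- Planned enrolment: 495.
- Rule: 10 patients per variable. Significance level, power and effect size do not enter.

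**Step 1. Reproduce the plan's figure.**
N × (1 + d) = 450 × 1.10 = 495. This matches exactly, so the increase is 10% of the required number, or 45 patients.

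**Step 2. Apply the stated loss to the stated enrolment.**
495 × (1 − 0.10) = 445.5, about 445 patients. The shortfall is 450 − 445.5 = 4.5, about 5 in whole patients. Relative to the minimum, 4.5/450 = 1.0%.

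**Step 3. Find the loss that 495 can absorb.**
1 − 450/495 = 45/495 = 9.09%. Any loss up to that rate leaves at least 450; the stated 10% does not.

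**Step 4. Find the enrolment that leaves 450 at 10% loss.**
N/(1 − d) = 450/0.90 = 500. Check: 500 × 0.90 = 450. The difference from the plan is 500 − 495 = 5 patients, or 5/500 = 1.0%.

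**Step 5. Express the result through the plan's rule (assumption).**
The number of variables is not given. If 450 is exactly 10 times the count, the count is 450/10 = 45, and 445.5 retained patients would support 445.5/10 = 44.55 variables. If the count were 44 or fewer and 450 had been rounded up, the need would be at most 44 × 10 = 440, and about 445 retained patients would still satisfy the rule.

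**The case against.** **The 10% may be an allowance on the required number.** The inflation formula is not stated, and 495 can be read as 450 plus 10% of 450; losing those 45 patients leaves 450. This reading is possible but less natural, because the text ties the increase to loss during follow-up, and such loss falls on enrolled patients. On that reading the loss actually allowed for is 9.09% of enrolment, so the sentence would still need clarifying.

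**The effect is negligible.** This stands. About 5 patients, or 1%, separate the figures, and no named analysis or conclusion would change between 445 and 450.

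**Much of the study does not depend on retention.** This also stands. The primary objective includes demographic, clinical and radiological characteristics. These are largely collected at baseline, so all 495 patients could contribute. Early neurological deterioration is assessed at 7 days. The shortfall touches mainly the 90-day and later outcomes, although these include the primary one.

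**Recruitment need not stop at 495.** The 450 is worded as a floor, and nothing makes 495 a ceiling.

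A reader might also infer three stronger claims that the document does not support:
- *Planned enrolment is below the minimum.* It is not: 495 exceeds 450 by 45. Only the number expected to remain after 10% loss falls short.
- *The design fails its own 10-per-variable rule.* This would need 45 variables, all of them used, and the full 10% loss. The 45 is an inference from 450/10, and Step 5 shows that a slightly smaller count would still be covered.
- *The study is underpowered.* The plan specifies no hypothesis for the primary outcome and no power or precision target, so there is none to miss.

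**Conclusion.** The sentence is wrong as written, and the correction is minor. At the stated 10% loss, 495 enrolled leaves about 445 patients with follow-up, about 5 (1%) below the stated minimum; 495 preserves 450 only when loss is at most 9.09%.

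This rests on one assumption, that the 10% is a share of enrolled patients, which is the ordinary meaning of loss during follow-up. It does not rest on the number of variables. No power or error rate is affected.

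**What to change.** Restate the sentence so that the three figures agree, in one of two ways:
- Keep 495 and state that it yields about 445 evaluable patients at 10% loss, or 450 at about 9% loss (495 × 0.91 = 450.45). This needs no extra patients.
- Give the target as 450/0.90 = 500, which adds 5 patients.

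Stating the number of variables in the same sentence would let a reader check the 450.

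Either option costs one sentence. For the second, the Current status section reports 143 patients from 16 August 2021 to 13 March 2022. That is 209 days, so 143/209 ≈ 0.68 patients per day, and 5 more patients would take 5/0.68 ≈ 7 days at that pace.

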### Statistical analysis

Categorical variables will be presented as frequencies and percentages, such as gender, vascular risk factors, lesions of penetrating artery, and therapies. Continuous variables with non-normal distributions will be shown as median and interquartile range (IQR), while continuous variables with normal distributions as mean and 95% confidence interval (CI), such as age, NIHSS score, blood pressure, and hemoglobin concentration. For the statistical significance analysis of the outcomes, Pearson χ 2 or Fisher’s exact test, Wilcoxon tests, and t-tests will be used, where appropriate, with statistical uncertainty expressed by means of 95% CI. Cox proportional hazards model, Logistic regression model, and Poisson regression model will be used to assess the association between outcomes and clinical or radiological predictors, where appropriate. The good prognosis is defined as 0–2 mRS score, and poor prognosis as 3–6 mRS score at 90 days. Predictors including clinical and radiological features and different treatments will be evaluated. All analysis will be performed using SAS 9.4 and two-sided *P* < 0.05 is considered significant.

### Data management

As mentioned above, the metadata of BAD-study are stored in the structured eCRF via internet, with central monitoring dynamically. Only anonymous data will be provided to researchers. In addition, data monitoring committee is not needed in this observational study.

### Current status

The first patient of BAD-study was enrolled on August 16, 2021, after thorough assessment by the board. Until March 13, 2022, our ongoing study has recruited 143 patients. The brief demographic and clinical data of eligible patients are shown in Table3.

**Table 3 Tab3:** Baseline characteristics of patients enrolled in BAD-study

Characteristic	Total
Overall, no.	143
Age, years, mean (95%CI)	59.6 (25.9–93.3)
Female sex, no. (%)	44 (30.8)
Types of stroke onset, no. (%)	
Ischemic Stroke	140 (97.9)
TIA	2 (2.1)
History of stroke, no. (%)	35 (24.5)
Ischemic stroke	33 (23.1)
TIA	1 (0.7)
Cerebral hemorrhage	1 (0.7)
History of hypertension, no. (%)	82 (57.3)
History of diabetes mellitus, no. (%)	44 (30.8)
Elevated LDL-C (Self-report), no. (%)	3 (2.1)
Smoking, no. (%)	
Never	78 (54.5)
Ever	65 (45.5)
Regular drinking, no. (%)	
Never	100 (69.9)
Ever	43 (30.1)
NIHSS score at enrollment, median (IQR)	3 (2–6.3)
Hours from symptom onset to enrollment, median (IQR)	48 (30–65)

*CI* Confidence interval, *IQR* Interquartile range, *TIA* Transient ischemic attack, *NIHSS* National institute of health stroke scale

